### Sample-size calculations and interim analyses

The calculation of the sample size was based on our primary hypothesis that in AECOPD patients high-intensity NPPV leads to a reduced need for endotracheal intubation compared to low-intensity NPPV. Our previous clinical experience and previous studies [18–20] led us to anticipate that the need for endotracheal intubation would be 15% for the low-intensity NPPV group. Based on the assumption that the need for intubation could be reduced to 6% in the high-intensity NPPV group, we estimated that a minimum sample size of 480 patients would be required to detect a between-group difference of 9% for the need for intubation, with an 81% power and a two-tailed alpha level of 0.05, using superiority tests for two proportions. Assuming a dropout rate of 20%, we calculated that 600 patients should be enrolled.

Interim analysis to assess superiority is scheduled, and it will take place at hospital discharge of the first 300 randomized patients. The criteria for premature discontinuation of the study, based on the results of this single interim analysis, will be those defined by O’Brien and Fleming [34]. It will be performed at the coordinating center by an independent data and safety monitoring board (DSMB). The DSMB will meet by conference call, and DSMB discussions will take place by email or conference call.

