### Statistical analysis

We will report continuous variables as means ± standard deviations or medians and interquartile ranges, when appropriate, and categorical variables as proportions.

Continuous variables will be compared using an appropriate parametric (Student’s *t* test) or nonparametric (Mann–Whitney *U* test) method. Categorical variables will be compared using a chi-square test or Fisher’s exact test, if appropriate. A linear mixed model with two factors (study group and time) will be used to analyze variables repetitively measured over time; Bonferroni’s adjustment for multiplicity of tests will be used in post hoc comparisons to ensure that the total error rate will not exceed 0.05.

We will use a chi-square test or Fisher’s exact test to compare the primary outcome and secondary dichotomous outcomes, and a parametric (Student’s *t* test) or nonparametric (Mann–Whitney *U* test) method to compare secondary continuous outcomes, as appropriate. For the primary and secondary outcomes, we will calculate between-group differences in risk for dichotomous outcomes, between-group median differences (using Hodges–Lehmann estimates) for continuous outcomes with non-normal distributions, and between-group mean differences for continuous outcomes with normal distributions, all with 95% confidence intervals. The baseline characteristics will be tested for imbalance. If imbalances are found (despite the 1:1 randomization of a relatively large cohort), the primary and secondary outcome variables will be analyzed using a multiple logistic regression model, adjusted for possible baseline imbalances.

Cumulative event rates for the primary and secondary endpoints involving time-to-event data will be estimated for the two groups using the Kaplan–Meier method and compared using a log-rank test. Hazard ratios, their 95% confidence intervals, and *P* values for the comparison of the two treatment groups will be determined using the Cox regression model.

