In case of loss to follow-up or consent withdrawal, the causes will be reported. Intention-to-treat (ITT) and per protocol (PP) analyses will be conducted. For the ITT analysis, data will be processed for all trial patients in the groups in which they were randomized. A PP analysis will be performed as a sensitivity analysis in the case of any loss to follow-up, a missing primary endpoint, or any protocol deviation that might lead to a biased conclusion. Missing data will be handled using the “last observation carried forward” method.

All tests will be two-sided. Differences with *P* values of less than 0.05 will be considered statistically significant, except for those incorporating multiple comparisons. Statistical analyses will be performed using SPSS software (version 19.0, SPSS Inc., Chicago, IL, USA).

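### The stated 81% power does not follow from the stated inputs: 480 patients give about 90% power for 15% versus 6%, and 81% needs only about 372

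*Protocol article*

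**What the plan says.** The protocol article, under Sample-size calculations and interim analyses, expects that "the need for endotracheal intubation would be 15% for the low-intensity NPPV group" and assumes that "the need for intubation could be reduced to 6% in the high-intensity NPPV group". From this it derives, as a minimum, that "480 patients would be required to detect a between-group difference of 9% for the need for intubation, with an 81% power". Alpha is two-tailed 0.05, and the method is described as superiority tests for two proportions, with no margin given. A 20% dropout allowance then raises 480 to 600.

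Randomization and blinding gives 1:1 allocation. Statistical analysis names a chi-square or Fisher's "exact test to compare the primary outcome and secondary dichotomous outcomes". It also says: "For the ITT analysis, data will be processed for all trial patients in the groups in which they were randomized".

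**The concern.** The article prints every input of a two-proportion calculation (both rates, alpha, sidedness, allocation, sample size and power), so the result can be checked without any other source. Halving 480 and applying the standard formula gives power near 90%, not 81%.

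At least one printed element must therefore be wrong or incomplete: the 6%, the 480, the 81%, or the implied null of no difference. A reader cannot tell which.

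- If 81% is right, the trial was sized for a different effect or hypothesis from the one printed.
- If 6% and 480 are right, the type II error risk at the design effect is about 10%, not 19%. A null result would then be stronger evidence against a 9-point reduction than the stated power implies.

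The figure also bears on whether 600 patients are justified.

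**Working it through.** **Inputs.** p1 = 0.15, p2 = 0.06, difference d = 0.09, two-sided alpha 0.05 (z = 1.960), 480 patients in total (all from Sample-size calculations and interim analyses); 1:1 allocation (Randomization and blinding), so n = 240 per arm; chi-square or Fisher's exact test (Statistical analysis).

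**Step 1: the figure that reproduces.** Dropout: 480 / (1 − 0.20) = 600, as stated.

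**Step 2: power at 240 per arm, pooled two-proportion test.**

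- Mean rate = (0.15 + 0.06)/2 = 0.105
- SE under the null = √(2 × 0.105 × 0.895 / 240) = 0.0280
- SE under the alternative = √((0.15 × 0.85 + 0.06 × 0.94) / 240) = √((0.1275 + 0.0564) / 240) = 0.0277
- Power = Φ((0.09 − 1.960 × 0.0280) / 0.0277) = Φ(1.27) = **89.8%**

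**Step 3: the same inputs by other methods.**

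| Method, 240 per arm | Power |
|---|---|
| Pooled normal approximation | 89.8% |
| Unpooled normal approximation | 90.2% |
| Arcsine | 90.8% |
| Exact, chi-square test | 90.7% |
| Exact, chi-square with Yates correction | 87.8% |
| Exact, Fisher's test | 88.1% |
| One-sided 0.05, pooled (contradicts the text) | 94.4% |

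The lowest value is about 88%, still 7 points above the stated figure.

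**Step 4: sample size for 81% power.** With z = 0.878 for 81%:

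- n per arm = [1.960 × √(2 × 0.105 × 0.895) + 0.878 × √0.1839]² / 0.09² = (0.850 + 0.376)² / 0.0081 ≈ 186, or **372 in total**
- With continuity correction: 208 per arm, or 416 in total
- Excess of 480 over these: 480 − 372 = 108, and 480 − 416 = 64
- After 20% dropout: 372/0.8 = 465, and 416/0.8 = 520, against 600 stated

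For 90% power the pooled formula gives 484 and the unpooled formula 478. So 480 is close to the size for 90%.

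**Step 5: could the interim look explain it?** One O'Brien-Fleming look, with an assumed inflation factor of 1.008, takes 372 to 375. It does not account for 108 patients.

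**Step 6: which changes would bring 480 near 81%?**

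| Change | Power | Status in the article |
|---|---|---|
| 15% versus 7% | 80.2% | Contradicts both the 6% and the 9% difference |
| Superiority margin of 1 point | 81.8% pooled, 82.4% unpooled | No margin stated; the named tests have none |
| Dropout already taken from 480 (384 evaluable) | 82.3% | Dropout would be counted twice in reaching 600 |
| Two-sided alpha 0.02 | 81.6% | Contradicts alpha 0.05 |

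**Step 7: all 600 analysed.** At 300 per arm, power = Φ((0.09 − 1.960 × 0.0250) / 0.0248) = 95.1%, provided that every patient has an observed outcome and the rates hold.

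**The case against.** The arithmetic is not disputed. The other side argues mainly about importance.

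- **The error is conservative.** On its own assumptions the trial has more power than it claims, and no test, error rate or stopping rule uses the 81%. The interim rule is O'Brien-Fleming, and results will carry 95% confidence intervals, which matter more than planned power when a null result is read. This stands and limits the consequence: neither the analysis nor patient numbers are put at risk.
- **The design effect is stated plainly.** This is true of the printed text. But that effect, the 480 and the 81% cannot all hold, so the clear statement does not settle which effect was used.
- **An input may have been lost in condensing.** A superiority margin of about 1 point would nearly reproduce the figure, and the description of the method makes this plausible. That could explain the cause, but it does not rescue the text. The article presents its listed inputs as the basis of the calculation, and a chi-square or Fisher test has a null of no difference. If a margin was used, the sizing and the primary analysis address different hypotheses.
- **The 95.1% is a best case.** Missing data are to be filled by last observation carried forward, so patients who drop out may count as non-events and dilute the difference. This is fair, and the figure should be quoted only with its condition.

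**Conclusion.** The concern holds. On the stated inputs, power at 480 patients is 89.8% (about 88% to 91% across standard two-sided methods) against 81% printed, a gap of about 9 points. The size called a minimum exceeds what 81% requires by 108 patients, or by 64 with continuity correction. Choice of formula, rounding and the single interim look do not close the gap.

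The conclusion rests on equal arms of 240, the printed rates of 15% and 6%, two-sided alpha 0.05 and a null of no difference. The document does not show which element is wrong. Because the power is understated and not overstated, this is a wrong planning figure that needs correcting, not a sign of an under-sized trial.

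**What to change.** First establish from the original calculation which input produced 81%. Then amend the sentence in Sample-size calculations and interim analyses in one of two ways.

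1. **If 6%, 480 and a zero margin are right:** state that 480 evaluable patients give about 90% power to detect 15% versus 6% at two-sided alpha 0.05, and no longer call 480 a minimum for 81%. If power for all 600 is added (95%), say that it assumes complete outcome data.
2. **If another input was used** (a different rate in the high-intensity arm, a non-zero margin, a smaller alpha, or dropout already included in 480): state it and correct the figures that depend on it. If it was a margin, make the primary test and its null hypothesis match.

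The first route costs one corrected sentence. The second may also need a matching change in Statistical analysis, or in the dropout step if dropout was counted twice. The planned enrolment of 600 can stand.

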### Statistical analysis

We will report continuous variables as means ± standard deviations or medians and interquartile ranges, when appropriate, and categorical variables as proportions.

Continuous variables will be compared using an appropriate parametric (Student’s *t* test) or nonparametric (Mann–Whitney *U* test) method. Categorical variables will be compared using a chi-square test or Fisher’s exact test, if appropriate. A linear mixed model with two factors (study group and time) will be used to analyze variables repetitively measured over time; Bonferroni’s adjustment for multiplicity of tests will be used in post hoc comparisons to ensure that the total error rate will not exceed 0.05.

We will use a chi-square test or Fisher’s exact test to compare the primary outcome and secondary dichotomous outcomes, and a parametric (Student’s *t* test) or nonparametric (Mann–Whitney *U* test) method to compare secondary continuous outcomes, as appropriate. For the primary and secondary outcomes, we will calculate between-group differences in risk for dichotomous outcomes, between-group median differences (using Hodges–Lehmann estimates) for continuous outcomes with non-normal distributions, and between-group mean differences for continuous outcomes with normal distributions, all with 95% confidence intervals. The baseline characteristics will be tested for imbalance. If imbalances are found (despite the 1:1 randomization of a relatively large cohort), the primary and secondary outcome variables will be analyzed using a multiple logistic regression model, adjusted for possible baseline imbalances.

Cumulative event rates for the primary and secondary endpoints involving time-to-event data will be estimated for the two groups using the Kaplan–Meier method and compared using a log-rank test. Hazard ratios, their 95% confidence intervals, and *P* values for the comparison of the two treatment groups will be determined using the Cox regression model.

In case of loss to follow-up or consent withdrawal, the causes will be reported. Intention-to-treat (ITT) and per protocol (PP) analyses will be conducted. For the ITT analysis, data will be processed for all trial patients in the groups in which they were randomized. A PP analysis will be performed as a sensitivity analysis in the case of any loss to follow-up, a missing primary endpoint, or any protocol deviation that might lead to a biased conclusion. Missing data will be handled using the “last observation carried forward” method.

All tests will be two-sided. Differences with *P* values of less than 0.05 will be considered statistically significant, except for those incorporating multiple comparisons. Statistical analyses will be performed using SPSS software (version 19.0, SPSS Inc., Chicago, IL, USA).

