## Methods/design

### Aims

The primary aim of the HAPPEN study is to determine whether high-intensity NPPV is more effective for correcting hypercapnia than low-intensity NPPV in patients with AECOPD. The secondary aim is to determine whether high-intensity NPPV is more effective than low-intensity NPPV for decreasing PaCO_2_ from baseline to 2 h after randomization and hospital mortality, and improving 28-day mortality and 90-day survival.

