### Data collection and definitions

At each study center, patient data will be collected using that center’s dedicated pseudonymous CRF, and the CRFs will be stored in locked file cabinets in areas with limited access. Data will be transmitted to the coordinating center whenever a patient dies or is discharged from the hospital, and follow-up data will be transmitted to the coordinating center when follow-up is complete. In addition, the coordinating center will have direct access to the cloud platform to extract the data related to the NPPV parameters. Before the data are exported into a computerized database at the coordinating center, two trained data collectors from the coordinating center will check the completeness and quality of information. Logical checks will be performed for missing data and to determine inconsistencies. If required, the data collector will contact the investigator by phone to validate or reformat the data for entry into the database. Then all data entry will be performed separately by two trained data collectors, and their work will be checked by another two collectors. Only the principal investigator and the data managers at the coordinating center will have access to the final database.

At enrollment, patients’ baseline characteristics will be recorded: demographics, medical history, history of NPPV use, history of steroids and/or inhalation therapy use, smoking status, spirometry (forced ventilatory capacity and forced expiratory volume in 1 s), Acute Physiology And Chronic Health Evaluation (APACHE) II score, vital signs (including heart rate, RR, arterial blood pressure, SpO_2_), dyspnea score, scale for the use of accessory muscles, Glasgow coma scale (GCS) score, arterial blood gases (including pH, PaO_2_, PaCO_2_, bicarbonates, and lactates), and routine laboratory tests (including hemoglobin, white blood cell count, platelet count, prothrombin time, partial thromboplastin time, creatinine, blood urea nitrogen, alanine aminotransferase, aspartate aminotransferase, and bilirubin).

At 2, 6, 24, and 48 h after randomization, vital signs, dyspnea score, scale for the use of accessory muscles, GCS score, supplemental oxygen flow, and arterial blood gases will be recorded.

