### Endpoints and follow-up

The primary endpoint is the NPPV failure rate, defined as the need for endotracheal intubation and invasive ventilation at any point during the study. Secondary endpoints include decrement of PaCO_2_ from baseline to 2 h after randomization, hospital mortality, 28-day mortality, and 90-day survival, as well as actual intubation rate, intensive care unit (ICU) admission, hospital stay, hospital costs, ventilator-free days within 28 days, hospital-free days within 90 days, and 90-day hospital readmission.

All patients will be monitored until hospital discharge or until day 90 in cases where the patients remain at the hospital. After discharge, follow-up will be performed by phone on days 28 and 90 after randomization, and the following will be recorded: 28-day mortality, ventilator-free days within 28 days, hospital-free days within 90 days, 90-day survival, and 90-day hospital readmission.

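### The repeated-measures mixed model states no use of the enrollment value, so the supportive comparisons at 2 to 48 h lose precision that baseline adjustment would recover at almost no cost

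*Protocol article*

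**What the plan says.** The Statistical analysis section assigns one model to repeated variables: "A linear mixed model with two factors (study group and time) will be used to analyze variables repetitively measured over time". It continues: "Bonferroni’s adjustment for multiplicity of tests will be used in post hoc comparisons to ensure that the total error rate will not exceed 0.05". The text does not mention a group-by-time term, and it does not say how a pre-treatment value enters.

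Under Data collection and definitions, the enrollment record includes vital signs, dyspnea score, accessory-muscle scale, GCS and "arterial blood gases (including pH, PaO_2_, PaCO_2_, bicarbonates, and lactates". The same measures are then repeated: "At 2, 6, 24, and 48 h after randomization, vital signs, dyspnea score" and the rest of that list, which ends with arterial blood gases.

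Two other statements set the context. Under Aims, the primary aim is to "determine whether high-intensity NPPV is more effective for correcting hypercapnia than low-intensity NPPV in patients with AECOPD". Under Endpoints and follow-up, the only listed PaCO2 endpoint is at 2 h: "Secondary endpoints include decrement of PaCO_2_ from baseline to 2 h after randomization". As a secondary continuous outcome, it is assigned "a parametric (Student’s *t* test) or nonparametric (Mann–Whitney *U* test) method to compare secondary continuous outcomes, as appropriate".

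The one covariate adjustment in the section is a multiple logistic regression, used only if baseline imbalance is detected.

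**The concern.** Both arms start at an IPAP of 10 cmH2O and are titrated in steps of 1 to 2 cmH2O, up to 30 against 20 cmH2O. A sustained difference in PaCO2 or pH would therefore show in the 6, 24 and 48 h values, and the mixed model is the analysis assigned to repeated measures. It supports the stated aim of correcting hypercapnia beyond the single 2 h endpoint.

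A patient's PaCO2 or pH at enrollment is likely to predict later values. A model with group and time alone leaves that predictable variation in the error term. The imbalance-triggered adjustment does not fill the gap: a logistic model is for binary outcomes, and the gain from a prognostic baseline does not depend on observed imbalance. What is at stake is wider intervals and lower power in a supportive analysis. Validity is not in question.

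**Working it through.** **No figure to reproduce.** The article gives no SD, effect size or power for PaCO2 or for the mixed model. Its sample-size section concerns intubation only.

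**Inputs from the document.** Four post-randomization times (2, 6, 24, 48 h); 600 patients at 1:1, so 300 per arm; 480 before the 20% dropout allowance, so 240 per arm.

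**Assumptions not in the document.** SD 15 mmHg at every time, enrollment included; equal correlation rho between any two times, 0.6 with a range of 0.4 to 0.8; a constant difference of 3 mmHg over 2 to 48 h, or 4 mmHg at one time.

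**Standard-error unit.** 15 × √(2/300) = 1.225 mmHg; 15 × √(2/240) = 1.369 mmHg.

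**Average difference over the four post-baseline times**

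- Unadjusted variance factor: (1 + 3·rho)/4. At rho 0.6 this is 0.70.
- With the enrollment value as covariate: (1 + 3·rho)/4 − rho². At rho 0.6 this is 0.70 − 0.36 = 0.34.
- Power = Φ(3/SE − 1.96), with SE = unit × √factor.

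At rho 0.6:

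| Per arm | Analysis | SE (mmHg) | 3/SE | Power |
|---|---|---|---|---|
| 300 | unadjusted | 1.225 × √0.70 = 1.025 | 2.93 | 83% |
| 300 | covariate | 1.225 × √0.34 = 0.714 | 4.20 | 99% |
| 240 | unadjusted | 1.369 × √0.70 = 1.146 | 2.62 | 74% |
| 240 | covariate | 1.369 × √0.34 = 0.798 | 3.76 | 96% |

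The variance ratio is 0.34/0.70 = 0.49: the unadjusted average carries the information of about half the patients.

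Range at 300 per arm: at rho 0.4 the factors are 0.55 and 0.39, and power is 91% against 97–98%. At rho 0.8 they are 0.85 and 0.21, and power is 76% against more than 99%.

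**Difference at one time, 4 mmHg, Bonferroni over four comparisons (alpha 0.0125, critical value 2.498)**

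- Unadjusted factor 1. At 300 per arm: 4/1.225 = 3.27, power 78%.
- Covariate factor 1 − rho² = 0.64. At 300 per arm: 4/(1.225 × 0.8) = 4.08, power 94%.
- At 240 per arm: 66% against 88%.

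Counting enrollment as a fifth comparison (alpha 0.01) would lower the unadjusted figure only from 78% to 76%, so nearly all of the gap comes from not using the baseline.

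**If the post-baseline differences were read as change from enrollment.** The factor is (1 + 3·rho)/4 + 1 − 2·rho, which is 0.50 at rho 0.6. Power for 3 mmHg at 300 per arm is 93%, between the two figures above. At rho 0.4 the factor is 0.75, worse than unadjusted. The covariate form has the smallest variance of the three at each rho.

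**Conditional dilution.** Suppose enrollment were a fifth response level and only the group main effect were read. The expected difference at enrollment is zero under randomization, so a constant effect d is estimated as (0 + 4d)/5 = 0.8d, and 3 mmHg appears as 2.4 mmHg. With variance factor (1 + 4·rho)/5 = 0.68 and 300 per arm, 2.4/(1.225 × √0.68) = 2.38 and power is 66%. If enrollment is not a response level, a constant effect is not diluted.

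**The case against.** The strongest objection is that the sentence is condensed and the fault depends on how it is read. An interaction is a term between two factors, not a third factor, so a two-factor model can contain it. With only two study groups, Bonferroni-adjusted post hoc comparisons fit group contrasts at each time. The enrollment values are listed as baseline characteristics, apart from the four later times, so a four-level time factor is at least as natural as a five-level one. This stands. A reader might infer that the plan averages the pre-treatment value into its treatment effect, or that it cannot show the arms diverging. The document says neither: it does not exclude an interaction, does not make enrollment a response level, and does not name the group main effect as the reported estimate.

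A second objection is that such detail belongs in a statistical analysis plan, which is not shown, and that an unadjusted randomized comparison is valid. The validity point stands. The first part stands only partly, because the article does not leave the model open: it names the model's factors, the multiplicity method and an adjustment strategy, and the stated combination makes no use of a value already collected.

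A third is that the stakes are modest. This stands too. PaCO2 and pH at 6 to 48 h are not listed endpoints, no power is claimed for them, and the SD, effect and correlation above are assumed.

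**Conclusion.** The point holds as a loss of precision in a supportive analysis. The plan states a two-factor model and no use of the enrollment value, and its only adjustment does not apply to continuous repeated measures. If the 2 to 48 h values are compared without baseline adjustment, power for a 3 mmHg average difference is 83% against 99% at 300 per arm, or about 74% against 96% at 240 per arm. These figures rest on an assumed SD of 15 mmHg, equal correlation of 0.6 and complete data; the gap narrows at lower correlation and widens at higher.

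Dilution to 4/5 is a possibility that the wording permits, not something the plan states, and it should not be reported as what the trial will do. The comparison of NPPV failure and the test of the 2 h PaCO2 decrement are unaffected.

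**What to change.** Replace the mixed-model sentence under Statistical analysis with wording such as: *Values at 2, 6, 24 and 48 h will be the response in a linear mixed model with study group, time (categorical), group-by-time interaction and the enrollment value of the variable as fixed effects, and patient as the repeated unit. The between-arm difference at each of the four post-baseline times will be reported with confidence intervals, with Bonferroni adjustment over these four comparisons.*

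Variables with no enrollment value, such as the ventilator parameters, would use the same model without that covariate. The change should be fixed before unblinded data are examined.

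It needs no new data, because the enrollment values are already recorded. The cost is one sentence and a few extra model parameters. It also settles how enrollment and the interaction enter, which removes the dilution question.

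### Holm's step-down adjustment could replace Bonferroni in the repeated-measures post hoc comparisons: same error control, never less power, low materiality

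*Protocol article*

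**What the plan says.** The Statistical analysis section of the protocol article states: "A linear mixed model with two factors (study group and time) will be used to analyze variables repetitively measured over time". For the follow-up comparisons from that model, Bonferroni's "adjustment for multiplicity of tests will be used in post hoc comparisons", and the stated purpose is "to ensure that the total error rate will not exceed 0.05".

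The measurement times are in Data collection and definitions: "At 2, 6, 24, and 48 h after randomization, vital signs, dyspnea score", with arterial blood gases among the other items recorded at those times. The article does not say how many comparisons make up a family. It also does not say whether they are between arms, within arm over time, or both.

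The named endpoints are handled separately. Endpoints and follow-up lists the "decrement of PaCO_2_ from baseline to 2 h after randomization" among the secondary endpoints. A different paragraph of Statistical analysis gives a t test or Mann–Whitney U test as the "method to compare secondary continuous outcomes, as appropriate". The general rule is that P "values of less than 0.05 will be considered statistically significant", and the same sentence exempts tests that involve multiple comparisons.

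**The concern.** Bonferroni compares every P value in a family of m with 0.05/m, however many of the other comparisons have already been rejected. Once one null hypothesis has been rejected, fewer remain that could be true, and the error allowance can be shared among those. Bonferroni leaves that allowance unused; Holm uses it.

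What is at stake is modest. These comparisons show when, and for how long, the arms differ in blood gases, dyspnea and vital signs over 48 h. The Aims section puts correction of hypercapnia first, and a difference sustained over several time points is where the unused allowance costs most. No conclusion on NPPV failure, mortality or the other named endpoints depends on this choice.

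**Working it through.** **Inputs.** From the document: familywise limit 0.05, two-sided tests, post-randomization times 2, 6, 24 and 48 h. Assumed, because the document does not give them: m = 4 between-arm comparisons per variable (m = 5 if baseline is counted); 80% power for each real difference at unadjusted 0.05; correlation between the test statistics of 0, 0.5 or 0.7.

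**The plan's own figure.** Bonferroni with m = 4 tests each comparison at 0.05/4 = 0.0125, and 4 × 0.0125 = 0.05. With m = 5, 5 × 0.01 = 0.05. In 200,000 simulated sets with no real difference and m = 4, familywise error was 0.049, 0.043 and 0.036 at correlations 0, 0.5 and 0.7. The stated aim is met.

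**Holm's rule.** Order the P values and compare them in turn with 0.05/4 = 0.0125, 0.05/3 = 0.0167, 0.05/2 = 0.025 and 0.05, stopping at the first failure.
- *Same error limit.* Suppose m0 of the nulls are true. When the first true null is rejected, at most m − m0 others have been rejected before it, so it faced a threshold of at most 0.05/m0. By the Bonferroni inequality over the m0 true nulls, the probability of this is at most 0.05, whatever the correlation.
- *Never less power.* Every Holm threshold is at least 0.05/m, so whatever Bonferroni rejects Holm rejects too. The simulation found no exception.
- *Same first hurdle.* The smallest P value faces 0.05/m under both rules. The chance of at least one rejection, and the error when all nulls are true, are therefore identical.

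**Bonferroni power per real difference.** Φ(1.960 + 0.842 − 2.498) = Φ(0.304) = 0.62.

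**Comparison by simulation, m = 4** (Monte Carlo standard error about 0.1 percentage point):

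| Real differences among the four | Bonferroni | Holm, correlation 0 / 0.5 / 0.7 |
|---|---|---|
| All four | 62% | 73% / 71% / 70% |
| Two | 62% | 65% / 64% / 64% |
| One | 62% | 62% / 62% / 62% |

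With all four real, the chance of at least one rejection was 97.9%, 88.5% and 82.6%, the same for both methods. With two real, the error rate over the two true nulls was 0.021–0.025 for Bonferroni and 0.032–0.039 for Holm. Holm uses more of the allowance but stays below 0.05.

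**Sensitivity to family size.** With m = 5, Bonferroni gives 59%. Holm gives 68–70% if all five differences are real, 60–61% if two are, and 59% if one is.

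**The case against.** Bonferroni is a valid, pre-specified and conservative choice that achieves its stated purpose, and it is confined to post hoc comparisons. It also has simple simultaneous confidence intervals that agree with its tests. Holm does not, so an unadjusted 95% interval that excludes zero could stand beside a non-significant Holm-adjusted P value. The gain is largest when every difference is real and vanishes when only one is. All of this stands, and it makes the point an optional improvement and not the correction of an error. The interval argument weighs less here than it might, because the article promises 95% intervals for the primary and secondary outcomes but no simultaneous intervals for these comparisons.

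A reader might go further and infer that the 2-h PaCO2 difference falls under two conflicting thresholds: 0.05 as a secondary endpoint and 0.0125 as one time point of the mixed model. PaCO2 at 2 h can indeed appear in both analyses, but the text does not set them against each other. The endpoint has its own test in a separate paragraph, and the 0.05 rule exempts multiple-comparison tests. The endpoint is therefore judged by its own test at 0.05, and the model comparisons describe the course over time. Nor does the article say that the model's 2-h contrast is the same quantity as the decrement from baseline.

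**Conclusion.** The point holds as a cheap improvement of low materiality. For the same familywise limit of 0.05 and no added assumption, Holm is never less powerful than Bonferroni. With m = 4 and 80% unadjusted power, the gain per real difference is about 8–11 percentage points if all four differences are real, 2–3 if two are, and about none if one is. These sizes rest on an assumed family and an assumed power. The article gives neither the family size nor an SD or expected difference for PaCO2. That Holm is at least as powerful does not depend on those assumptions.

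It would be wrong to read this as saying that Bonferroni fails to control error, or that the plan contradicts itself over 2-h PaCO2. The primary endpoint and the tests of the named secondary endpoints are untouched.

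**What to change.** In Statistical analysis, name Holm's step-down adjustment instead of Bonferroni's for the post hoc comparisons from the mixed model, and keep the 0.05 limit on total error. The cost is one phrase of analysis wording. The procedure needs only the ordered unadjusted P values and no new data. The drawback to accept is that unadjusted 95% intervals would be shown beside Holm-adjusted P values, and a table note should say so.

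Optionally, add a sentence saying that the t or Mann–Whitney test alone decides the 2-h PaCO2 endpoint. This clarifies what the text already implies. Changing to Holm does not replace that sentence, because the smallest P value in a Holm family still faces 0.05/m.
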